### Study population

Children between 1 and 19 years of age with primary ALL, who are treated within the DCOG ALL-11 or subsequent study, are eligible for the TropicALL. Patients will be excluded if they are already using anticoagulant therapy upon screening, if they have active bleeding or a high risk for bleeding contraindicating anticoagulant therapy, including renal insufficiency (glomerular filtration rate (GFR) < 30 ml/min/1.73 m2), hepatic disease associated with coagulopathy leading to a clinically relevant bleeding risk, stage 2 hypertension defined as blood pressure confirmed >99th percentile +5 mmHg, if they have a heparin allergy or a history of heparin-induced thrombocytopenia (HIT), or any other condition that, judged by the investigator, would place the patient at increased risk of harm due to participation. Thrombocytopenia is no exclusion criteria. However, LWMH should be temporarily interrupted, if platelet levels drop below 20 × 10^9^/L.

### ALL-11 study design

All patients in ALL-11 are treated with a standardized treatment schedule. (Figs. 1, 2a and b.) All patients start with Induction IA and IB, after which patients are stratified according to their risk group. After risk group stratification, patients with Standard Risk ALL will be treated with cycle M, followed by cycle IV and maintenance therapy. Medium Risk group patients will be treated with cycle M, followed by Medium Risk Intensification and maintenance cycles. High Risk group patients will be treated with cycle M if identified by minimal residual disease (MRD) or with High Risk blocks if identified earlier. After three High Risk blocks, patients will undergo assessment for allogeneic stem cell transplantation eligibility, or will continue High Risk blocks. PEG-asparaginase is included in Induction IA (day 12, 26, 4; 1500 IU/m2) and, in case of continuous asparaginase treatment, IB (day 54, 68; individualized dose) and M (day 9, 23, 37, 51; individualized dose). In Medium Risk group patients (70% of all patients), PEG-asparaginase is administered every 2 weeks for 14 times or 8 times during Intensification, depending on the randomization between standard and continuous asparaginase treatment. Both arms have the same number of total PEG-asparaginase administrations.

**Fig. 1 Fig1:**
[figure not shown]
LMWH randomization in DCOG Protocol ALL 11, protocol 1A and 1B

**Fig. 2 Fig2:**
[figure not shown]
**a** LMWH randomization in DCOG Protocol ALL 11, MR intensification, without anthracyclines. **b** LMWH randomization in DCOG Protocol ALL 11, MR intensification, with anthracyclines

### Intervention; LMWH regimen

LMWH (nadroparin) will be given subcutaneously once daily, in a standardized prophylactic weight- and anti-Xa adjusted dose of 85 IU/kg with a maximum of 5700 IU/day [28]. Previous studies have indicated that especially young children require higher dosages of LMWH. Hence, peak anti-Xa levels should be measured, 3 to 5 days after start of LMWH prophylaxis, with an aimed anti-Xa level of 0.3–0.4 IU/ml [29]. Lidocain/prilocain cream can be applied to the skin locally for anesthesia before each subcutaneous injection. If nadroparin is not tolerated, other LMWHs can be administered according to local availability (Table 1). A registration booklet and registration of unused drugs will be used to monitor treatment compliance. The booklets will also include questions on the burden of daily subcutaneous injections.

**Table 1 Tab1:** Alternative LMWH schedule

LMWH	Dose
Enoxaparin	1 – 18y: 1 mg/kg once daily s.c
Dalteparin	65 ± 21.5 IE/kg once daily s.c
Tinzaparin	1 – 5y: 120 IE/kg once daily s.c.
	5 – 10y: 100 IE/kg once daily s.c.
	10 - 18y: 87.5 IE/kg once daily s.c.

### Data and blood sample collection

At the time of randomization for the TropicALL study and during the study, data will be collected from all patients, including baseline data, clinical risk factors for VTE, CVC characteristics, number of episodes of septicemia, asparaginase therapy and administration of other medications during ALL treatment.

Upon inclusion, one EDTA blood sample will be collected for evaluation of genetic thrombophilic mutations Factor V Leiden and Factor II mutation. Blood samples for coagulation assays, including antithrombin, fibrinogen, D-dimer, thrombin antithrombin complex (TAT) and thrombin generation, will be collected upon, during the induction cycle before the 2nd and 3rd asparaginase administration, and in Medium Risk group children in week 1 of Intensification and on the last day of PEG-asparaginase therapy of Maintenance. All coagulation assays will be performed at the end of the study. Blood collection dates coincide with other set sample collection dates in ALL-11 or subsequent study and will not form an extra burden for patients.

### Sample size calculation

Power calculations were based on an estimated symptomatic VTE incidence of 10% based on the previous DCOG ALL-10 study, and an estimated relative risk reduction (RRR) of 75% based on the abovementioned cohort studies with LMWH in childhood ALL [25, 26, 30, 31]. Using nQuery Advisor (7.0, 2007), it was calculated that 162 patients are required in each arm for a power of 80%, using a two-sided test with significance level α = 0.05. Hence, 324 patients will be randomized in this study.

### Randomization

Patients will be randomized to thromboprophylaxis with LMWH (arm A) or to no thromboprophylaxis (arm B, standard of care). Randomization will take place on day 11, which is the last day before the start of PEG-asparaginase administration during the induction cycle. A register of all patients, who were eligible but not included in the study, will be kept and reason for refusal of participation will be recorded. Randomization of each patient will be performed by a randomization computer program at the DCOG trial office and will be stratified to ensure equal distribution of patients over study arms. Stratification will be done according to type of ALL (B-cell or T-cell) and study center. The procedure will also guarantee concealment of allocation by the treating physician.

### Treatment arms in TropicALL

All patients randomized to arm A will receive LMWH from the day asparaginase is started, until 28 days (for PEG-asparaginase) after the end of asparaginase therapy, in all treatment cycles with asparaginase (Induction cycle, Intensification in Medium Risk protocol). In case PEG-asparaginase is replaced by Erwinia asparaginase, LMWH will be given until 7 days after the last administration of Erwinia asparaginase. Patients treated according the medium risk arm of the protocol will receive 34 weeks (=238 days) of LMWH in the induction and intensification cycles, while patients treated according to the standard risk and high risk ALL-11 protocols will receive LMWH in the induction cycle only (=42 days during and after asparaginase). Patients in arm B, the standard of care arm, will not receive any form of thromboprophylaxis.

LMWH should be stopped 24 h before interventions, i.e. lumbar puncture or CVC insertion, and should be restarted after invasive procedures or surgical interventions within 24 h, provided the clinical situation allows. Moreover, LMWH should be temporarily interrupted if platelet levels drop below 20 × 10^9^/L, and in case of major bleeding.

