### Statistical analysis

All data will be analyzed according to the intention-to-treat principle. Descriptive data will be presented as mean with its corresponding standard deviation if normally distributed, and medians with ranges if data are skewed. Depending on the data distribution the Student’s *t* test or a Mann-Whitney U-test will be used to compare continuous variables between the treatment groups. Categorical variables will be analyzed using the Chi-square test.

Efficacy and safety of LMWH to prevent VTE will be analyzed by the difference between the incidence proportions and cumulative incidences of the primary efficacy and safety outcomes, symptomatic objectified VTE and major or clinically relevant non-major bleeding, respectively, observed from randomization up to 14 and 7 days after the last PEG asparaginase and Erwinia asparaginase, respectively. A two-sided test with significance level α = 0.05 will be used.

All bleeding events that occur during LMWH or within 2 days after cessation of LMWH will be included. Incidence proportions (number of children with outcome during the period divided by number of children at risk at the beginning of the period) and cumulative incidences will be estimated by a joint model to estimate event free survival for the primary safety outcome. To identify which risks factors are associated with time to VTE a joint model for longitudinal data and survival outcome will be used.

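### The 28-day LMWH tail after PEG-asparaginase does not give the stated totals of 42 and 238 treatment days; a 14-day tail gives both exactly

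*Protocol article*

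**What the plan says.** All of the following is in the protocol article.

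- **Treatment arms in TropicALL, the rule.** LMWH starts on the first day of asparaginase and continues "until 28 days (for PEG-asparaginase) after the end of asparaginase therapy". This applies in every covered cycle, listed as induction and, for medium risk, intensification. For Erwinia asparaginase the tail is 7 days.
- **Treatment arms in TropicALL, the totals.** Medium-risk patients "will receive 34 weeks (=238 days) of LMWH in the induction and intensification cycles". Standard- and high-risk patients "will receive LMWH in the induction cycle only (=42 days during and after asparaginase").
- **ALL-11 study design.** Induction IA has PEG-asparaginase on day 12, day 26 and a third day that reads as 4 in the text at hand. For medium risk, "PEG-asparaginase is administered every 2 weeks for 14 times or 8 times during Intensification", depending on a separate randomization between standard and continuous asparaginase.
- **Data and blood sample collection.** Samples are taken "during the induction cycle before the 2nd and 3rd asparaginase administration", so induction has a third dose.
- **Statistical analysis.** Outcomes are observed from randomization "up to 14 and 7 days after the last PEG asparaginase and Erwinia asparaginase", respectively.

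**The concern.** The tail and the totals are two statements of the same quantity: how long a child in arm A receives daily anticoagulant injections. They stand in one paragraph and give different answers. A reader who stops LMWH by the rule and a reader who stops it by the totals would differ by 14 days in each covered course on the standard schedule.

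The outcome window is affected as well. If 28 days is intended, LMWH continues for 28 - 14 = 14 days beyond the point after the last PEG dose at which the general outcome window closes. A VTE in those last 14 treated days would fall outside the stated analysis window.

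**Working it through.** **Inputs**

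- Dose interval: 14 days (ALL-11 study design).
- Induction: three doses. Days 12 and 26 are legible. Day 40 is inferred for the third, because it fits the 14-day spacing and the later continuous-schedule doses in "IB (day 54, 68; individualized dose) and M (day 9, 23, 37, 51; individualized dose") carry on at days 54 and 68. Day 4 is impossible, since the Randomization section places the start of PEG-asparaginase after day 11.
- Intensification, medium risk, standard schedule: 14 doses.
- Tail *t*: 28 days as stated, 14 days as the alternative.

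**Formula**

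Days of LMWH per course = (number of doses - 1) × 14 + *t*. Courses are summed.

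**Reproducing the plan's totals**

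| Group (standard schedule) | Formula | *t* = 14 | *t* = 28 | Stated |
|---|---|---|---|---|
| Standard/high risk, induction only | 2 × 14 + *t* | 42 | 56 | 42 |
| Intensification alone | 13 × 14 + *t* | 196 | 210 | not stated |
| Medium risk, both courses | 28 + 182 + 2*t* | 238 | 266 | 238 |

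Both stated totals come out exactly with a 14-day tail. Equivalently, 3 × 14 = 42 and (3 + 14) × 14 = 238, that is, 14 days of LMWH per dose. The conversion of 34 weeks to 238 days is correct (34 × 7 = 238).

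**Size of the difference under the 28-day rule**

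- Standard/high risk: 56 - 42 = 14 days, 14/42 = 33%.
- Medium risk, standard schedule: 266 - 238 = 28 days, 28/238 = 12%. The total would be 266/7 = 38 weeks.

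**Check without the inferred day**

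Use only induction days 12 and 26. Induction is then at least 14 + 28 = 42 days and intensification is 210, so medium risk is at least 42 + 210 = 252 days. That already exceeds 238 by 14, and a later third dose can only lengthen it.

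**Counting convention**

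Counting the end day adds one day per course. With a 28-day tail this gives 57 and 268, further from the stated totals. With a 14-day tail it gives 43 and 240, so the exact match is with the end day not counted.

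**Comparison with the outcome window**

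| Preparation | LMWH tail | Outcome window after last dose |
|---|---|---|
| Erwinia asparaginase | 7 days | 7 days |
| PEG-asparaginase | 28 days | 14 days |

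The Erwinia pair agrees and the PEG pair does not.

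**The case against.** **238 alone does not force a 14-day tail.** If the 28-day tail followed only the final end of asparaginase therapy, medium risk would total 28 + 182 + 28 = 238 (day 40 inferred). This stands as far as it goes. It sits badly with a rule stated for all covered cycles, and it leaves standard/high risk at 28 + 28 = 56, not 42. For the same reason, one cannot simply take 238 - 42 = 196 as the intensification share: the 42 days are stated only for standard and high risk.

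**A two-dose induction would give 42 with a 28-day tail** (14 + 28). The blood-sampling schedule names a third induction dose, and the medium-risk total would still be 252 on the standard schedule. On the continuous schedule the two-dose induction can be made to reach 238 (42 + 70 for cycle M + 126 for eight intensification doses). That also requires leaving the IB doses uncovered and giving LMWH in cycle M, which is not among the listed cycles. No reading that keeps to the text yields both totals with 28 days.

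**The evidence is incomplete.** The third induction day is inferred, and the two schedule figures are not shown. Both are true. The figures 56 and 266 rest on day 40; the lower bound of 252 does not.

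**Bleeding is already covered.** A reader might infer that bleeding in the last 14 treated days would be lost. The documents do not support this: the Statistical analysis section separately includes all bleeding during LMWH and up to 2 days after it stops. Late VTE is also still recorded, since monitoring runs through all cycles plus 3 months. What remains is that such a VTE lies outside the stated analysis window.

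**The totals may be only descriptive, and this is a condensed article.** Nothing shows that sites dosed from it. That limits the practical effect but does not remove a contradiction between two printed statements.

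**Conclusion.** The 28-day PEG tail and the totals of 42 and 238 days are inconsistent as written. On the standard schedule, with day 40 inferred, the rule exceeds the totals by 14 days (standard/high risk) and 28 days (medium risk). With legible induction days only, the medium-risk excess is at least 14 days.

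A reader might go further and conclude that 28 is simply a misprint for 14. The exact match of both totals and the 14-day outcome window point that way, but the text does not establish it; the totals could have been computed from a superseded tail. Nor does anything here bear on power or on the estimated treatment effect: the sample size does not use the treatment duration. The point should be fixed because it concerns how long children receive a daily anticoagulant.

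**What to change.** The sponsor confirms the intended tail after PEG-asparaginase, and the text is then aligned in one of two ways.

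- **If 14 days is meant:** change 28 to 14 in the section on treatment arms. The totals of 42 and 238 stay, and the outcome window needs no change on this account. Cost: one number.
- **If 28 days is meant:** restate the totals as 56 days (standard/high risk) and 266 days (medium risk, standard asparaginase schedule), and state the total for the continuous schedule separately. Extend the efficacy and safety window under Statistical analysis to at least 28 days after the last PEG dose, so that it covers the treated period. Cost: two corrected totals, one added total and one changed window.

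Neither option needs new data, since VTE monitoring already extends 3 months past the ALL treatment cycles.

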### Safety measures

If major bleeding occurs, the following measures should be considered: (1) delay the next LMWH administration or discontinue treatment, (2) consider protamine sulfate administration, (3) consider usual treatment for bleeding, including blood transfusion, and/or fresh frozen plasma, (4) measure anti-Xa level of LMWH. If bleeding cannot be controlled, consider administration of recombinant factor VII (Novoseven®) or prothrombin complex concentrate.

### Reporting of symptomatic VTE events

Patients are monitored for clinical symptoms of VTE during all treatment cycles of ALL-11 and a 3-month follow-up period. To establish systematic registration of symptomatic VTE, events must be prospectively centrally recorded on special VTE reporting forms in the CRF. VTE reporting forms include several specifications of the VTE to enable complete analysis of the event and its consequences for the patient and ALL treatment. For each symptomatic, objectively diagnosed VTE event in a study patient, a VTE reporting form should be completed and returned to the DCOG Office within 14 days after the event. Recurrent VTE should also be recorded.

Presence, replacement, removal or reinsertion of a CVC should be documented in the CRF, as well as the applied method of catheter flushing.

### Statistical analysis

All data will be analyzed according to the intention-to-treat principle. Descriptive data will be presented as mean with its corresponding standard deviation if normally distributed, and medians with ranges if data are skewed. Depending on the data distribution the Student’s *t* test or a Mann-Whitney U-test will be used to compare continuous variables between the treatment groups. Categorical variables will be analyzed using the Chi-square test.

Efficacy and safety of LMWH to prevent VTE will be analyzed by the difference between the incidence proportions and cumulative incidences of the primary efficacy and safety outcomes, symptomatic objectified VTE and major or clinically relevant non-major bleeding, respectively, observed from randomization up to 14 and 7 days after the last PEG asparaginase and Erwinia asparaginase, respectively. A two-sided test with significance level α = 0.05 will be used.

All bleeding events that occur during LMWH or within 2 days after cessation of LMWH will be included. Incidence proportions (number of children with outcome during the period divided by number of children at risk at the beginning of the period) and cumulative incidences will be estimated by a joint model to estimate event free survival for the primary safety outcome. To identify which risks factors are associated with time to VTE a joint model for longitudinal data and survival outcome will be used.

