### Withdrawal of patients

Children can discontinue their participation in the study at any time for any reason if they wish to do so without any consequences for their care, at their own request or at the request of their parents/legally acceptable representative. Furthermore, study medication can be stopped prematurely in case of serious adverse events, VTE requiring therapeutic anticoagulant treatment, or if, in the investigator’s opinion, study medication should be stopped for any other reason.

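### As the only bleeding analysis, intention-to-treat combined with an on-LMWH event rule understates the bleeding risk while on LMWH; a supportive treatment-received analysis should stand beside it

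*Protocol article*

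**What the plan says.** All statements come from the protocol article.

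- **Principle** (Statistical analysis): "All data will be analyzed according to the intention-to-treat principle". Safety is not excepted.
- **Incidence proportion** (same section): "number of children with outcome during the period divided by number of children at risk at the beginning of the period". Having received LMWH is not a condition for being counted. Neither being at risk nor the period is defined specifically for bleeding.
- **Bleeds counted** (same section): "All bleeding events that occur during LMWH or within 2 days after cessation of LMWH will be included".
- **Observation window for efficacy and safety** (same section): "observed from randomization up to 14 and 7 days after the last PEG asparaginase and Erwinia asparaginase, respectively".
- **Control arm** (Treatment arms in TropicALL): "Patients in arm B, the standard of care arm, will not receive any form of thromboprophylaxis".
- **Planned end of LMWH** (same section): "until 28 days (for PEG-asparaginase) after the end of asparaginase therapy". Medium-risk patients are planned to receive 238 days of LMWH, the others 42 days.
- **Early stopping** (Withdrawal of patients): "study medication can be stopped prematurely in case of serious adverse events", and also for VTE needing therapeutic anticoagulation or for any other reason the investigator sees.
- **Exposure records** (Intervention; LMWH regimen): a registration booklet, and "registration of unused drugs will be used to monitor treatment compliance".

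**The concern.** Counting unexposed children as treated is conservative for efficacy, because it makes a benefit harder to show. For harm it works the other way: it makes an excess of bleeding harder to see.

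The on-LMWH event rule adds to this. If it restricts which arm A bleeds count, a child who never starts cannot supply an event yet can still be in the denominator. A child who stops early stays in the denominator as a full child after the time when an event could count.

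Safety of LMWH is part of the stated aim, and the Discussion intends the results to support (inter)national guidelines. The Sample size calculation section sizes the trial on VTE only, so sensitivity to a bleeding difference was not planned for. Some departure from treatment is foreseeable: medium-risk children, given as 70% of all patients, face 34 weeks of daily injections, and the article acknowledges that burden.

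**Working it through.** **1. The plan's own figure.** The article states 162 per arm for symptomatic VTE of 10%, a 75% relative reduction (so 10% × 0.25 = 2.5% in arm A), two-sided 0.05 and 80% power. The pooled-variance formula for two proportions without continuity correction gives 163 per arm, and 162 per arm gives 79.9% power. The figure reproduces. It says nothing about bleeding, for which the article gives no figure.

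**2. Dilution formulas.** Let c be the bleeding risk off LMWH, a the risk on LMWH, and f the share of arm A never exposed.

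- Intention-to-treat, all bleeds counted: arm A risk = (1 − f)a + fc, so the excess over arm B is (1 − f)(a − c).
- Only on-LMWH bleeds counted, over all assigned: arm A risk = (1 − f)a, so the excess is (1 − f)a − c.

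Both excesses equal a − c at f = 0 and shrink as f grows, provided a > c. The second shrinks faster.

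**3. Numbers.** The documents give none of c, a or f; all three are assumptions. With c = 2%, a = 8% and 162 per arm, the table shows exact power of the uncorrected chi-square test at two-sided 0.05.

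| f | Excess, all bleeds (points) | Power | Excess, on-LMWH bleeds only (points) | Power |
|---|---|---|---|---|
| 0% | 6.0 | 73% | 6.0 | 73% |
| 2% | 5.9 | 72% | 5.8 | 71% |
| 5% | 5.7 | 69.5% | 5.6 | 68% |
| 10% | 5.4 | 66% | 5.2 | 63% |
| 20% | 4.8 | 58% | 4.4 | 52% |
| 30% | 4.2 | 49% | 3.6 | 40% |

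Example at f = 10%: 0.9 × 8% + 0.1 × 2% = 7.4%, and 7.4% − 2% = 5.4 points. With on-LMWH bleeds only, 0.9 × 8% = 7.2%, and 7.2% − 2% = 5.2 points.

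With c = 3% and a = 9%, intention-to-treat power is 64% at f = 0 and 56% at f = 10%. With c = 1% and a = 2%, it is 10% and 9%.

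**4. Early stoppers.** The formulas treat f as children with no exposure at all. Suppose instead that a share s stops halfway, with risk spread evenly over the course. Each such child carries about (a + c)/2, so the excess is (1 − s/2)(a − c). With s = 10% this is 0.95 × 6.0 = 5.7 points, the same as 5% never exposed. A child who stops because of a bleed already has the event and dilutes nothing.

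**5. The windows side by side.** For PEG-asparaginase the general window closes 14 days after the last dose. The LMWH rule can run to 28 + 2 = 30 days in arm A and has no counterpart in arm B. The last two columns of the table therefore mix two things: the denominator, and counting arm A only on drug while arm B is counted in full. The extra loss there cannot be put down to the denominator alone.

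**The case against.** The strongest reply is that intention-to-treat is the right randomized comparison for the policy of offering prophylaxis, which is what a guideline needs. That stands. A reader might infer that intention-to-treat is simply the wrong or biased method for bleeding here. The article does not support this: the shortfall arises only when the quantity wanted is the risk while on LMWH.

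Second, the article does not clearly fix an all-assigned denominator for bleeding. If the period were LMWH exposure, a non-starter would not be at risk in it. The planned cumulative incidences from a model could also censor off-drug time. This stands too. The all-assigned denominator is the natural reading of the intention-to-treat sentence with the incidence-proportion definition, but not the only one.

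Third, non-exposure may be small. Randomization is on day 11, the last day before asparaginase, which leaves little time to fail to start. Interruptions for procedures or low platelets belong to the regimen and are not non-adherence. A reader might take the 49% or 40% power at 30% non-exposure as the expected loss. Nothing in the article supports 20–30% never exposed, nor a fourfold bleeding excess; its Background expects negligible bleeding. If bleeding is that rare, the number of events limits the safety conclusion far more than the choice of population does.

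Fourth, a supportive safety set is often left to the full protocol or analysis plan, and one may exist there. Its absence from an article would be no finding. The point rests on what the article does state: one rule for all data, next to an on-treatment event rule that does not fit it.

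**Conclusion.** The point holds in a limited form. The article applies intention-to-treat to bleeding and also ties counted bleeds to LMWH exposure. On the natural reading of the two, unexposed children and off-drug time can add to the arm A denominator but not to the events. If that is the only bleeding analysis, the risk while on LMWH is understated, in the direction of no harm. The direction needs only the assumption that LMWH raises bleeding.

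The size cannot be derived from the documents. Under an assumed 2% versus 8% and 162 per arm, the loss is modest where non-exposure is low: power of 73% falls to about 72–70% at 2–5% never exposed and to 66% at 10%. Early stoppers cost less than these figures. The case for changing the plan is that the correction is cheap and the error reassuring, not that a large distortion has been shown.

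**What to change.** In the Statistical analysis section:

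1. Keep the intention-to-treat bleeding comparison, over one observation window defined identically in both arms, and reconcile it with the asparaginase-based and LMWH-based windows now written.
2. Add a supportive treatment-received analysis. Arm A would be the children with at least one LMWH dose. On-LMWH bleeds (to two days after cessation) would also be expressed per child-time on LMWH, taken from the booklet and unused-drug records. The comparison is with arm B over the matching asparaginase periods. Arm A non-starters are not moved into arm B.
3. State that both analyses are reported before any conclusion on safety is drawn.

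The cost is a short change of wording and one more table, since exposure is already to be recorded. The downside is that the treatment-received comparison is not fully protected by randomization, so it supports the intention-to-treat result and does not replace it.

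### Randomization is stratified by ALL type and centre, but the only test named for categorical outcomes is an unstratified chi-square test: valid, slightly conservative, and improvable at no cost

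*Protocol article*

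**What the plan says.** The Randomization section of the protocol article states: "Stratification will be done according to type of ALL (B-cell or T-cell) and study center".

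The Statistical analysis section does not mention these strata again. Its first paragraph covers descriptive summaries and general group comparisons, and ends with "Categorical variables will be analyzed using the Chi-square test". The next paragraph says that efficacy and safety will be assessed by the "difference between the incidence proportions and cumulative incidences of the primary efficacy and safety outcomes", and adds: "A two-sided test with significance level α = 0.05 will be used". That paragraph names no specific test and does not say which of the two measures decides the trial.

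The Sample size calculation section starts from an "estimated symptomatic VTE incidence of 10% based on the previous DCOG ALL-10 study" and a 75% relative risk reduction. From these, "it was calculated that 162 patients are required in each arm for a power of 80%, using a two-sided test with significance level α = 0.05".

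**The concern.** Stratified allocation keeps the arms balanced on ALL type, so differences in risk between B-cell and T-cell patients add almost nothing to the true variance of the treatment contrast. The plain chi-square test does not use this. Its variance is computed from the pooled risk and still contains the between-stratum part. If VTE risk depends on ALL type, that variance is too large, p-values are somewhat too big, and intervals built on the same variance are somewhat too wide.

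At stake is a little power in a trial planned at 80%, with no margin above it. The stratum variables needed to recover it are already recorded for randomization.

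**Working it through.** **1. The plan's own figure.** Inputs from the Sample size calculation section: control risk 0.10; risk under LMWH 0.10 × (1 − 0.75) = 0.025; two-sided α 0.05; power 80%. The pooled risk is (0.10 + 0.025)/2 = 0.0625. For an ordinary two-proportion test without continuity correction:

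n = [1.960 × √(2 × 0.0625 × 0.9375) + 0.8416 × √(0.10 × 0.90 + 0.025 × 0.975)]² / 0.075² = (0.6710 + 0.2846)² / 0.005625 ≈ 162.3 per arm.

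This is 163 rounded up, against the stated 162. Power at 162 per arm is 79.9%. The continuity-corrected version gives 189 and the one-sided version 128, so neither is what was used. The planned size is therefore that of an unstratified two-proportion test.

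**2. Expected events.** 162 × 0.10 + 162 × 0.025 = 16.2 + 4.05 = 20.25.

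**3. How conservative the unstratified test is.** The article gives neither the T-cell share nor VTE risk by ALL type. Assume a 15% T-cell share and hold overall control risk at 10%. The B-cell risk is then (0.10 − 0.15 × T-cell risk)/0.85. Under the null hypothesis, chi-square uses a per-patient variance of 0.10 × 0.90 = 0.090. With allocation balanced within type, the correct figure is the within-type average, 0.15 × pT(1 − pT) + 0.85 × pB(1 − pB). The approximate true size is 2 × [1 − Φ(1.96/√ratio)], where ratio is the within-type variance over 0.090.

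| T-cell risk | B-cell risk | Risk ratio | Within-type variance | Ratio | Approximate size |
|---|---|---|---|---|---|
| 10% | 10% | 1 | 0.0900 | 1.000 | 0.050 |
| 20% | 8.2% | 2.4 | 0.0882 | 0.980 | 0.048 |
| 30% | 6.5% | 4.6 | 0.0829 | 0.922 | 0.041 |
| 40% | 4.7% | 8.5 | 0.0741 | 0.824 | 0.031 |

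**4. Simulation of the same scenarios, stratifying by type only** (162 per arm; 40,000 to 100,000 trials per scenario; size shown as the range over repeated runs where they differ):

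| T-cell risk | Size, chi-square | Size, CMH | Power, chi-square | Power, CMH | Gain (points) |
|---|---|---|---|---|---|
| 10% | 0.051 | 0.051 | 82.5% | 82.5% | 0 |
| 20% | 0.049 | 0.050 | 82.7% | 83.1% | 0.4 |
| 30% | 0.042–0.043 | 0.049–0.050 | 82.8% | 84.4% | 1.6 |
| 40% | 0.031–0.033 | 0.050–0.051 | 83.8% | 86.8% | 3.0 |

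Simulated power lies above the 79.9% of step 1 because that formula is a normal approximation and events are few.

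**5. Adding every centre as a stratum.** The article does not give the number of centres. With 7 assumed, type by centre makes 14 strata, or 20.25/14 ≈ 1.4 expected events each. Two sets of 100,000 simulated trials, with blocks of 4 and 15% T-cell, compare chi-square with CMH by type and centre:

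- Equal centres with no centre effect, T-cell risk 20%, 30%, 40%: power 83.0% vs 82.8%, 83.4% vs 84.1%, 84.3% vs 86.3%. The change is −0.2, +0.7 and +2.0 points.
- Centre risks also varying (T-cell odds ratio 1, 2, 3, 5; centre SD on the logit scale 0, 0.3, 0.5, 0.8): power 82.9% vs 82.6%, 83.2% vs 83.0%, 83.3% vs 83.4%, 83.6% vs 84.6%. The change is −0.3 to +1.0 points. Chi-square size is 4.9%, 4.8%, 4.6% and 3.9%; CMH size is 4.9% to 5.0%.

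Stratifying by type costs nothing when risks are equal. Stratifying fully by centre as well can cost a few tenths of a point.

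**The case against.** The strongest reply has four parts.

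- **The sentence is general.** It closes a paragraph on descriptive data and is not expressly tied to the VTE comparison. That is so. Chi-square is nevertheless the natural reading for a comparison of incidence proportions, it matches the sample size, and nothing in the section replaces it.
- **Adjustment is detail for the full protocol or the SAP, which are not shown.** Silence alone would indeed be no finding. Here the article names an unstratified test, so the point is a better method than the one stated, not a missing detail. A stratified analysis may already be specified elsewhere.
- **The design never counted on a gain from stratification.** This stands. The 162 per arm and the chi-square test agree with each other, and the sample size is not called into question.
- **The larger gains rest on extreme assumptions.** This also stands. T-cell risks of 30% and 40% require 4.6 and 8.5 times the B-cell risk, and the risk factors listed in the Background do not include ALL type.

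A reader might infer that ignoring the strata breaks control of type I error. It does not: the departure is towards conservatism in every scenario where risks differ, so a positive result would not be undermined. A reader might also infer that centre differences add to the gain. The simulations do not support that in general: with about 20 events, strata for every centre add little and may cost slightly.

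**Conclusion.** The mismatch between stratified allocation and an unstratified named test is real, and its consequence is small. The chi-square test is valid. With an assumed 15% T-cell share and T-cell control risk of 20% to 30%, its true size is about 0.049 to 0.043, and about 0.4 to 1.6 power points are lost against a test stratified by type. The loss is nil if risks are equal, and reaches 3.0 points only in the extreme 40% case. All of this rests on assumed T-cell shares and risks, since the article gives neither. It is a minor point: a free improvement, not an error in the validity or size of the trial.

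**What to change.** State in the Statistical analysis section that the single primary test compares the VTE incidence proportion by a two-sided Cochran-Mantel-Haenszel test at α = 0.05, stratified by ALL type. Include centre only after pooling by a rule written down before the data are seen. Report the Mantel-Haenszel risk difference with its 95% CI.

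Label cumulative incidence as supportive. This also settles a separate ambiguity, that one test is announced for two measures.

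The cost is one or two sentences. The strata are already recorded for randomization, and no change to sample size or data collection is needed. If the full protocol or SAP already specifies this, aligning the article's wording is enough.
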